#### Secondary outcomes: effectiveness and safety outcomes

The secondary outcome of effectiveness is incident opioid overdose, defined as participant-reported overdose responding to community-administered naloxone, overdose requiring emergency medical services, or fatal overdose. Fatal overdoses will be ascertained through: (1) review of the San Francisco Medical Examiner records, (2) review of emergency medical services records and hospital systems within San Francisco, and (3) participant emergency contacts who will be contacted if participants miss consecutive study visits. Secondary safety outcomes include the proportion of participants experiencing grade 2 or higher adverse events at least possibly related to study medication, including injection site reactions, hepatic abnormalities, and other adverse events. Grade 2 adverse events are defined as moderate events requiring minimal intervention (e.g., nausea), while grades 3–5 represent severe, life-threatening, or fatal events requiring significant intervention (e.g., opioid overdose) [18]. 

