#### Randomization and blinding

Following eligibility confirmation and obtaining written informed consent, participants will be randomized 1:1 to either intramuscular naltrexone or usual care using a computer-generated randomization sequence with random block sizes. Participants and clinicians will not be blinded to treatment assignment, but laboratory personnel conducting biomarker analyses will remain blinded to treatment allocation.

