#### Baseline assessments

At screening, participants will undergo comprehensive evaluation including medical history, physical examination, and DSM-V assessment for substance use disorders [15]. Laboratory testing will include complete blood count, comprehensive metabolic panel, and HIV testing for those reporting HIV-negative status. For participants who report living with HIV, status will be confirmed through medical records or documentation. Prior to enrollment, participants will complete informed consent that includes detailed discussion of randomization, medical risks and medical record review, and education regarding the investigational nature of naltrexone for overdose prevention.

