#### Follow-up assessments

Monthly follow-up visits will include clinical assessment, adverse event monitoring, and collection of biomarkers. At weeks 12 and 24, participants will undergo additional laboratory testing including complete blood count and comprehensive metabolic panels. All participants, regardless of study completion or early discontinuation, will be offered assistance to receive provider-prescribed naltrexone at study conclusion which is possible via public insurance in California. A final assessment at week 32 will evaluate incident overdoses and adverse events via telephone interview.

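### The emergency-service and hospital record search is assigned to fatal overdoses only, so non-fatal overdoses, which are part of the effectiveness outcome, have no systematic source apart from open-label participant report

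*Protocol article*

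**What the plan says.** All references are to the Protocol article.

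- **Outcome.** The section on secondary outcomes defines incident opioid overdose as "participant-reported overdose responding to community-administered naloxone, overdose requiring emergency medical services, or fatal overdose". Only the first component names where the information comes from, namely the participant.
- **Sources.** The next sentence lists them but opens with deaths: "Fatal overdoses will be ascertained through: (1) review of the San Francisco Medical Examiner records, (2) review of emergency medical services records", the second item also taking in hospital systems. The third source on the same list is "participant emergency contacts who will be contacted if participants miss consecutive study visits".
- **Blinding.** Under Randomization and blinding: "Participants and clinicians will not be blinded to treatment assignment". Only laboratory staff are blinded.
- **Later contact.** Under Follow-up assessments: "A final assessment at week 32 will evaluate incident overdoses and adverse events via telephone interview".
- **Consent.** Under Baseline assessments, the consent discussion includes "detailed discussion of randomization, medical risks and medical record review". It is not limited to deaths.
- **Use of the result.** The Discussion says that the trial will supply baseline overdose incidence for powering a definitive trial.

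**The concern.** EMS and hospital records are the natural source for overdoses that bring out an ambulance. The article plans to search those records but ties the search to fatal events. The non-fatal EMS component therefore sits in the outcome without a source, and the community-naloxone component is self-reported by design.

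Two things are at stake. First, what participants report, and whether they stay in contact to report it, may depend on an arm that they know. An overdose may itself lead to loss of contact. With about 5 to 6 events expected in usual care, a few unseen events matter. Second, even equal under-capture in both arms lowers the usual-care incidence, which is a stated product of this pilot.

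**Working it through.** **1. Components against sources**

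| Outcome component | Source named in the article |
|---|---|
| Reversed by community naloxone | Participant report |
| Non-fatal, needing EMS | None |
| Fatal | Medical Examiner; EMS and hospital records; emergency contacts |

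The only other enquiry aimed specifically at overdose is the week 32 telephone interview, which is also self-report. The sources that do not depend on the participant are thus all attached to the third row.

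**2. The plan's own figure**

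The article gives no figure for ascertainment. The one stated figure that depends on the overdose count is in Sample size and power: 80% power for 4.72 usual-care events (12% over 24 weeks) against 0. With n per arm, risks p1 and p2, and p̄ their mean, the pooled normal approximation is

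power = Φ{ [(p1 − p2) − z·√(2p̄(1 − p̄)/n)] / √[p1(1 − p1)/n + p2(1 − p2)/n] }.

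- 12% v 0%, n = 50, two-sided 0.05: (0.12 − 1.96 × 0.0475)/0.0460 = 0.59, so power is 72%. One-sided, it is 82%.
- 4.72/50 = 9.44% v 0%, n = 50: 61% two-sided, 72% one-sided.

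The 80% is approached only one-sided with 12% of 50, which is 6 events and not 4.72 (4.72/0.12 = 39.3 participants). That mismatch is a separate matter. It is noted here because 12% in 50 participants is used as the starting point below.

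**3. What under-capture would do (illustration)**

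Inputs: 50 per arm and a true usual-care risk of 12% (both from Sample size and power), with 0 events on naltrexone. The fraction of events unseen, m, is an assumption, because the documents give none.

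With 50 per arm and 0 events on naltrexone, the two-sided Fisher p-value is 0.027 for 6 v 0 and 0.056 for 5 v 0. Six observed events is therefore a convenient marker. The observed count X is binomial with n = 50 and risk 0.12(1 − m):

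| m | Observed risk | Expected events | P(X ≥ 6) |
|---|---|---|---|
| 0 | 12.0% | 6.0 | 0.565 |
| 0.10 | 10.8% | 5.4 | 0.458 |
| 0.20 | 9.6% | 4.8 | 0.347 |
| 0.35 | 7.8% | 3.9 | 0.192 |

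The second column is also the incidence that would be carried forward to the definitive trial.

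**4. Unequal capture (illustration)**

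Suppose that there is no true effect and that capture is 70% in one arm and 90% in the other, both assumed. The apparent risk ratio is then 0.70/0.90 = 0.78, or 0.90/0.70 = 1.29 if the arms are reversed.

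**The case against.** The strongest reply is that this is silence in a condensed article and not a plan to rely on self-report. Participant report is attached only to the community-naloxone component, consent covers record review without limit, and the EMS and hospital systems will be searched anyway. Part of this stands: the article does not prescribe self-report for non-fatal EMS events, and the fuller protocol may be broader. But the article does more than omit detail. It states an ascertainment rule and limits it to deaths. If a wider search is intended, the sentence misstates it and still needs correcting.

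A reader might infer four stronger things, none of which the document supports.

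- **That non-fatal events are known only at attended visits, or are simply lost in people who drop out.** The week 32 telephone interview asks about overdoses away from a visit. Calls to emergency contacts and the search for deaths could also bring some non-fatal events to light. Loss is a risk, not a certainty.
- **That follow-up is censored at last contact, so that censoring is informative.** The Effectiveness analysis section names Kaplan-Meier and Cox methods but gives no censoring rule. That may properly sit in the analysis plan.
- **That the plan expects a 25-point retention gap.** That figure is the difference detectable with the stated power. Moreover, one of the listed acceptability measures is retention in treatment, and stopping injections is not the same as losing overdose follow-up.
- **That the calculation demonstrates bias.** Table 3 shows lost sensitivity under assumed miss rates, and Fisher's test is not the planned overdose analysis. Even with full capture the chance of 6 or more events is only 56%, so much of the fragility comes from sample size.

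**Conclusion.** The point holds as one of scope. The sentence on sources limits the EMS and hospital search to fatal overdoses, and no source is named for non-fatal overdoses needing EMS, although they count towards the outcome. In an open-label trial this leaves non-fatal events without a systematic source that is independent of the participant's own report. Under-counting is possible, and so is under-counting that differs by arm; neither is established.

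The size depends on assumptions. If 10% to 35% of usual-care events went unseen, a true 12% would appear as 10.8% to 7.8%, and the chance of 6 or more observed events would fall from 56% to between 46% and 19%. This is a secondary outcome in a pilot whose primary outcome is acceptability, so the trial's main conclusion is not at risk. The sentence should nevertheless be corrected, because the incidence estimate is meant to be reused and the correction is cheap.

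**What to change.** Reword the sources sentence under Secondary outcomes so that the EMS and hospital record review covers non-fatal as well as fatal overdoses. It should apply to every randomised participant in both arms, from randomisation to week 24, regardless of visit attendance.

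Keep the full composite as the effectiveness outcome. Alongside it, analyse the record-ascertained events (EMS-attended or fatal) over that common window as a sensitivity analysis. Using one window for all participants avoids mixing components that are observed for different lengths of time after contact is lost.

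The cost is modest extra abstraction from records already to be searched, and the consent discussion already includes medical record review. Two gaps remain: non-fatal events outside San Francisco, and community-naloxone events without EMS, would still depend on self-report.

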**Methods:**

Acceptability (primary outcome) will be assessed quantitatively through retention at 24 weeks and proportion of on-time injections, and qualitatively through in-depth interviews (*n* = 35). Effectiveness (secondary outcome) includes incident opioid overdose events requiring medical attention or community naloxone. Safety includes grade 2 or higher adverse events. Opioid exposure patterns (exploratory outcome) will be assessed through monthly urine toxicology, hair samples analyzed via liquid chromatography/mass spectrometry, and Timeline Followback interviews. Analysis will use Kaplan-Meier methods for time-to-event outcomes and mixed methods for implementation evaluation.

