## Methods

### NOD study design

This 24-week pilot randomized controlled trial will evaluate intramuscular naltrexone for opioid overdose prevention among individuals living with or at risk for HIV who use stimulants. The study will enroll 100 participants randomized 1:1 to receive either monthly intramuscular naltrexone (380 mg) or usual care, and both groups will receive harm reduction services.

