#### Intervention

Participants randomized to the intervention arm will receive monthly intramuscular naltrexone 380 mg administered in the ventrogluteal region. Both intervention and usual care arms will receive standard harm reduction services including naloxone, safer consumption supplies, and fentanyl test strips. All participants will undergo monthly clinical assessments and biomarker collection for the evaluation of substance use throughout the 24-week study period.

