### Assessment & data collection

#### Overview

The study will assess outcomes across three categories, aligned with our primary, seconday, and exploratory objectives. The primary outcome is acceptability of intramuscular naltrexone, evaluated through both quantitative implementation metrics and qualitative interviews with participants in both arms. Secondary outcomes include effectiveness (incident opioid overdose events requiring medical attention or community naloxone administration) and and safety including grade 2 or higher adverse events. The exploratory outcome characterizes patterns of opioid exposure via monthly point-of-care urine toxicology, hair analysis for substance exposure via liquid chromatography-tandem mass spectrometry (LC-MS/MS)-based methods, and Timeline Followback interviews [17]. 

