#### Effectiveness analysis (Secondary)

Time-to-event analysis using Kaplan-Meier methods will evaluate cumulative probability of first opioid overdose. Cox proportional hazards models will estimate overdose risk adjusting for key covariates including age, race/ethnicity, housing status, and HIV status. Safety analyses will compare the proportion of adverse events between arms using exact methods for binary outcomes and regression models for continuous safety measures.

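### The safety outcome is limited to drug-related events, which usual care cannot have, so the plan must say which adverse events the between-arm comparison counts

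*Protocol article*

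**What the plan says.** Four places in the protocol article describe the safety outcome or its analysis.

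- **Secondary outcomes: effectiveness and safety outcomes** gives the full definition, the "proportion of participants experiencing grade 2 or higher adverse events at least possibly related to study medication", and continues "including injection site reactions, hepatic abnormalities, and other adverse events".
- **Effectiveness analysis (Secondary)** gives the analysis: "Safety analyses will compare the proportion of adverse events between arms using exact methods for binary outcomes".
- **Overview**, under assessment and data collection, has "safety including grade 2 or higher adverse events", with no relatedness condition.
- **Abstract, Methods** has "Safety includes grade 2 or higher adverse events", again with no relatedness condition.

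Three further statements fix what the arms receive and who knows the allocation. Under NOD study design, participants are "randomized 1:1 to receive either monthly intramuscular naltrexone (380 mg) or usual care". Under Intervention, "Both intervention and usual care arms will receive standard harm reduction services including naloxone, safer consumption supplies, and fentanyl test strips". Under Randomization and blinding, "Participants and clinicians will not be blinded to treatment assignment"; only the laboratory staff who run the biomarker assays are blinded. No placebo injection is described, and no rule is given for judging relatedness in the usual care arm.

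**The concern.** A participant who is never given the study medication cannot have an event related to it. The same holds, even more plainly, for injection site reactions. If the outcome as defined goes into the between-arm test, the usual care numerator is therefore fixed at zero before any data are collected.

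Two consequences follow. First, background illness is no longer subtracted. Randomization lets the control arm show how many grade 2 or higher events would have occurred anyway, and a numerator fixed at zero discards that information. Second, the naltrexone numerator depends on unblinded clinicians deciding whether an event is possibly related, which is a low threshold. The comparison would then measure attribution practice as much as toxicity, and it could not show a lower event risk on naltrexone if there were one.

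Safety is one of two named secondary outcomes, and the Introduction says that the risks and benefits of this use are unknown. An interpretable between-arm safety estimate is therefore worth having.

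**Working it through.** The article states no rate, power or sample size for the safety comparison, so there is no figure to reproduce. The point is logical; the arithmetic only shows its possible size.

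**Step 1: set the sections together.** The definition counts participants with a grade 2 or higher event judged at least possibly related to study medication. The study medication is naltrexone. Usual care gets none, and the naloxone given to both arms is presented as a harm reduction supply. Under this definition the control count is 0/50 whatever happens to those participants; any control event counted would contradict the definition.

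**Step 2: how many attributed participants give p < 0.05 against 0/50?** Inputs: 50 per arm (Sample size and power). A two-sided 0.05 level is assumed; the article states α = 0.05 for retention only and does not give the sidedness. With equal arms and a zero control count, the two-sided Fisher p is 2 × C(50, x) / C(100, x).

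- x = 5: 2 × 2,118,760 / 75,287,520 = 0.056
- x = 6: 2 × 15,890,700 / 1,192,052,400 = 0.027

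Six participants (6/50 = 12%) are enough.

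**Step 3: how often would that happen with no true excess?** Assume the same true risk r of at least one grade 2 or higher event in both arms, and that a share f of affected naltrexone participants is judged possibly related. The attributed count is then binomial with n = 50 and probability q = r × f. The result needed is P(X ≥ 6). Neither r nor f is in the article, so a range is shown.

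| Risk r (assumed) | Share f (assumed) | q | P(X ≥ 6) |
|---|---|---|---|
| 20% | 25% | 0.05 | 3.8% |
| 20% | 50% | 0.10 | 38% |
| 20% | 100% | 0.20 | 95% |
| 30% | 25% | 0.075 | 17% |
| 30% | 50% | 0.15 | 78% |
| 40% | 25% | 0.10 | 38% |
| 40% | 50% | 0.20 | 95% |

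**Step 4: the all-cause comparison for contrast.** With equal true risk of 20%, 30% or 40% in both arms and every grade 2 or higher event counted regardless of cause, the two-sided Fisher test at 50 per arm gives p < 0.05 in 2.8%, 3.1% and 3.2% of trials. The rate stays below 5% and hardly moves with the background risk.

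**The case against.** The strongest reply is that no sentence says the related-only proportion is what will be tested between arms. The definition is introduced as something the safety outcomes include, so it need not be the whole list. The analysis sentence, the Overview and the abstract carry no relatedness condition. An all-cause comparison, with the related-only figure as one reported item, may be what was meant. The two shorter statements can also be read as condensed versions of the definition and not as rivals to it. This stands in part: the link between definition and test is the natural reading but not an explicit one, so the point is put conditionally. It does not remove the need for a change, because a reader who follows the only full definition arrives at the structural zero.

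The illustration also has limits. The risks and attribution shares are assumed. At 20% risk with a quarter attributed, the chance is 3.8%, below the nominal level. The 95% figure at 20% risk requires every affected naltrexone participant to be counted as possibly related. No safety decision is tied to a p-value.

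A reader might infer three stronger things that the article does not support.

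- **Harms judged unrelated are lost.** They are not. Adverse events are assessed at every visit and again by telephone at week 32, blood count and metabolic panel are repeated at weeks 12 and 24, and the monitoring board reviews all serious adverse events. At most, such events are absent from this one summary.
- **The exact test would be run on events and ignore repeats within a person.** The analysis sentence speaks loosely of a proportion of events, but it refers to binary outcomes and the definition counts participants. No test on event counts is planned.
- **The effectiveness outcome is built into the safety count.** Opioid overdose appears only as an example of a grade 3 to 5 event. Under the related-only definition, it would count only if judged possibly related to naltrexone.

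**Conclusion.** The concern holds in conditional form. If the outcome defined under the secondary outcomes is the one compared between arms, the usual care rate is zero by construction, and the comparison reflects open-label attribution instead of excess harm. Because the abstract and the Overview omit the relatedness condition, the article does not settle which set of adverse events is compared.

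The size depends on figures that the article does not give. Over assumed risks of 20% to 40%, with a quarter to a half attributed, the chance of a nominally significant excess when none exists runs from 3.8% to 95%. That spread is the useful message: the answer would be driven by how relatedness is judged. The documents do not support saying that a false harm finding is likely, or that the plan explicitly commits to the flawed test.

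This is a should-fix item. Safety is a secondary outcome in a 100-person pilot, and no sample size, efficacy conclusion or numerical stopping boundary in the article rests on this test.

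**What to change.** Use one definition in the abstract, the Overview, the secondary outcomes section and the analysis section:

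1. **Between-arm comparison:** the proportion of participants in each arm with at least one grade 2 or higher adverse event of any cause, with an exact confidence interval for the difference.
2. **Naltrexone arm only, descriptive:** the proportion with events at least possibly related to study medication, and the proportion with injection site reactions.

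The cost is wording. Adverse events are already assessed at every four-weekly visit, with no restriction by arm, so no new data are needed. One limit remains: with open-label treatment, reporting of milder events may still differ between arms, and the write-up should say so.

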#### Exploratory outcome: exposure assessment and biomarkers

To characterize patterns of opioid exposure, we will collect both short-term and long-term biomarkers at monthly visits. Urine will be tested using a CLIA-waived enzyme immunoassay. Hair samples will be analyzed at the UCSF Hair Analytical Laboratory using a validated panel that enables assessment of substance exposure (e.g. all opioids, cocaine, methamphetamine) via LC-MS/MS-based methods over sequential monthly intervals. These objective measures will be paired with Timeline Followback interviews to assess discordance between self-reported and biological measures of exposure.

#### Follow-up assessments

Monthly follow-up visits will include clinical assessment, adverse event monitoring, and collection of biomarkers. At weeks 12 and 24, participants will undergo additional laboratory testing including complete blood count and comprehensive metabolic panels. All participants, regardless of study completion or early discontinuation, will be offered assistance to receive provider-prescribed naltrexone at study conclusion which is possible via public insurance in California. A final assessment at week 32 will evaluate incident overdoses and adverse events via telephone interview.

